## Abstract

**Background:**

Prone position ventilation is a widely used lung protection ventilation strategy. The strategy is more convenient to implement in children compared to adults. Due to the precise mechanism of improving oxygenation function, development of pediatric prone ventilation technology has been largely focused on children with acute respiratory distress syndrome. There is a paucity of high-quality studies investigating the effects of prone position ventilation after pediatric cardiac surgery. The purpose of this study is to evaluate the feasibility and effectiveness of prone position ventilation in infants who develop postoperative acute lung injury after surgery for congenital heart disease.

**Methods:**

A single-center, randomized controlled trial of pediatric patients with acute lung injury after surgery for congenital heart disease who will receive prone position ventilation or usual care (control group). A total of 68 children will be enrolled according to the inclusion criteria. The main outcome measures will be lung compliance and oxygenation index. The secondary outcomes will be duration of mechanical ventilation, length of stay in cardiac intensive care unit, reintubation rate, and complication rate.

**Discussion:**

This study will investigate the feasibility and effectiveness of prone position ventilation techniques in children who develop postoperative acute lung injury after surgery for congenital heart disease. The results may help inform strategies to improve airway management after surgery for congenital heart disease.

**Trial registration:**

ClinicalTrials.gov NCT04607993. Initially registered on 29 October 2020.

## Background

Prone position has been used to treat severe hypoxemia in patients with acute respiratory distress syndrome (ARDS) since the 1970s. According to a systematic review, use of the prone position during mechanical ventilation improved survival of patients with ARDS who received protective lung ventilation [1]. Pediatric acute lung injury (PALI) is a common complication of congenital heart disease that presents with refractory hypoxemia. Currently, mechanical ventilation is one of the main methods for the treatment of PALI. Most data regarding management in children are extrapolated from clinical trials conducted in adults or neonates. According to a recent study, only 10% of patients with PARDS receive prone positioning. There are no studies in pediatrics to support regular use of prone positioning in PALI [2]. Prone position ventilation refers to placement of the patient in the prone position during mechanical ventilation to facilitate lung expansion in the atelectatic area and improve the ventilation-perfusion ratio. Critically ill pediatric patients represent a special group, and postural therapy plays an important role in the management of airways of these patients.

Prone position ventilation promotes lung recruitment and improves gas exchange through its effects on pleural pressure and lung compression [2]. Prone position ventilation can reduce the difference between the dorsal and ventral pleural pressure, thereby improving the uniformity of lung ventilation and reducing alveolar hyperinflation and alveolar collapse. This results in improved ventilation and oxygenation, and many patients can maintain this improvement even after switching back to the supine position for ventilation [3, 4]. Studies have demonstrated that prone positioning can significantly improve the oxygenation index of newborns [5], reduce the airway resistance in preterm infants, increase the tidal volume inhaled per unit time, improve the dynamic lung compliance, increase the respiratory efficiency of preterm infants, and reduce the occurrence of apnea [5, 6]. In a study of PARDS, prone position was found to increase the tidal volume and thoracic mobility compared with the supine position [7].

In the supine position, both heart and diaphragm compression may aggravate the collapse of the gravity-dependent area of the lung and worsen hypoxemia and ventilator-related lung injury [8]. During ventilation in the prone position, the heart becomes a gravity-dependent zone, which reduces the pressure on the lung tissue in the middle of the dorsal side. In addition, studies have found no significant effect of prone position on the heart rate, hemodynamics, and cerebral vascular oxygen supply [9].

During mechanical ventilation in the supine position, the effect of posture and sedative muscle relaxants adversely affects the sputum drainage. However, in the prone position, the gravitational force helps improve the sputum drainage [10].

With the advances in cardiac diagnosis and treatment technology, patients undergoing treatment of congenital heart disease tend to be younger and have lower body weight. Maintenance of the respiratory function after cardiac surgery in infants and young children is a key determinant of successful surgical outcomes. Owing to the complexity of cardiac surgery and the prolonged operative time, cardiac surgery is performed under low temperature cardiopulmonary bypass; this increases the risk of hypoxemia after cardiopulmonary bypass. In infants and young children, use of cardiopulmonary bypass increases the pulmonary blood flow and reduces lung tissue compliance. High concentration of oxygen in the medium and the impaired thoracic integrity caused by the surgical incision can easily lead to postoperative hypoxemia [11]. Different degrees of lung injury may occur after cardiac surgery. In our department, the incidence of postoperative pulmonary complications is 11.3%, of which the incidence of atelectasis, VAP, and lung consolidation is 8.2%, 1.4%, and 0.80 %, respectively. Delay in the correction of hypoxemia and lung injury in children may lead to adverse life-threatening outcomes. In such settings, early mechanical ventilation in the prone position can improve the blood oxygen content and alleviate ventilator-related lung injury. At the same time, timely and effective respiratory management and lung physical therapy can be performed to correct hypoxemia. Increase in the partial pressure of blood oxygen can reduce complications and facilitate weaning of the patient from the ventilator. Due to the safety of cardiac surgery, only a few studies [12] have investigated the effect of prone position ventilation for patients with hypoxia after cardiac surgery.

Fineman et al. [13] found no significant differences between the prone position and the supine position in terms of air leakage, enteral nutrition, sedation, or analgesia. Prone positioning caused no hemodynamic instability or arrhythmia; moreover, no serious incidents (such as deintubation) occurred during the process of changing positions. Regarding the start time of prone ventilation after cardiothoracic surgery, Eremenko et al. [14] studied patients who had undergone cardiac surgery with a median chest incision. Prone ventilation was started from 3.6 ± 1.2 days after surgery and lasted for 4–12 days. It was found to significantly improve the pulmonary function and arterial oxygenation within hours. Thus, prone positioning seems to be an effective intervention to improve arterial oxygenation in patients who develop ARDS after cardiovascular surgery.

Studies have shown that prone ventilation is not contraindicated in patients after cardiac surgery [15]. Studies [16] have also shown that prone position ventilation can be used in patients with respiratory failure, ALI, respiratory distress syndrome, and other diseases; moreover, prone position can also be used after apnea, gastroesophageal reflux, and cardiopulmonary bypass surgery. Studies conducted overseas have also demonstrated the feasibility of prone position ventilation in patients after cardiac surgery [17].

Prone position ventilation technology is a widely used lung protection ventilation strategy in clinical settings. Compared with adults, it is more convenient to implement in children. Due to the precise mechanism of improving oxygenation function, development of pediatric prone position ventilation technology is largely focused on pediatric patients with ALI. There is a paucity of high-quality studies investigating the effect of prone position ventilation after pediatric cardiac surgery. Determining the indications for prone position ventilation after surgery and standardization of the process (including the position angle and the prone duration) is a key research imperative. The increasing complexity of surgery for congenital heart disease and the decreasing trend in the age of children undergoing surgery have increased the risk of postoperative pulmonary complications. Therefore, development of prone position ventilation technology for critically-ill children with congenital heart disease is a key imperative in order to reduce postoperative pulmonary complications and shorten the duration of mechanical ventilation.

## Trial objectives

The trial objectives are as follows: to assess the effectiveness and feasibility of prone position ventilation for infants with PALI after surgery for congenital heart disease, to compare the effects of conventional lying position and prone position ventilation on the outcomes of infants with acute lung injury after surgery for congenital heart disease, and to provide a basis for prone position treatment in these children.

## Methods

### Trial design

This study will be a single-center prospective randomized controlled study enrolling infants with postoperative PALI after surgery for congenital heart disease at the Children's Hospital of Fudan University (Fig. 1).

**Fig. 1 Fig1:**
[figure not shown]
Flow chart providing an overview of important trial steps. First, understand the research situation and methods of this study at home and abroad through the literature, and then conduct a pre-test, correct the research deviation through the pre-test, and randomly group according to the allowance standard, determine the intervention group and the control group, and conduct data collection. Entry and statistical analysis

## Participants and recruitment

### Inclusion and exclusion criteria

A total of 68 infants who qualify the following criteria will be included in the study:
PALI after surgery for congenital heart disease or patients in whom chest X-ray and CT findings indicate PALI. The diagnostic criteria for PALI: (1) acute onset; (2) hypoxemia, oxygenation index ≥ 4; and (3) chest radiograph showing bilateral lung infiltratesInvasive mechanical ventilationAge range: 0–12 monthsPatients with stable hemodynamic status, more than 72 h after surgery. Hemodynamic stability defined as Inotropes stable (IS < 10) or based on ECHO (ejection fraction > 50%)Informed consent of family membersThis study has been approved by the Ethics Committee of the Children’s Hospital of Fudan University, No. (2020) 130

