**Table Taba:** 

Inclusion criteria	Exclusion criteria
**- Pediatric patients with lung injury after** surgery for **congenital heart disease or** those in whom **chest X-ray** and **CT** findings indicate the need for augmenting pulmonary drainage due to **pulmonary complications**.	-Hemodynamic instability, severe hypotension, ventricular arrhythmia - Pacemaker dependent - ECMO
**- Invasive mechanical ventilation**	-Intracranial hypertension
**-**Age range: **0–12 months**	-Active acute bleeding
**-Stable hemodynamics, more than 72 h after surgery**	-Spinal injuries and untreated unstable fractures, orthopedic surgery or recent abdominal surgery
**-Informed consent of family members**	-Facial trauma
	Severe pneumothorax
	-Patients with delayed chest closure and wound infection requiring immobilization

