### Intervention strategies

The family members of the subjects will be informed about the purpose and methods of prone position ventilation, and their consent will be obtained for participation in the study.Careful assessment of the disease status will be performed and adequate fixation of the various cannulas and vascular catheters will be ensured.Enteral nutrition will be suspended 30 min before and the gastrointestinal nutrition tube will be closed before preparing for prone positioning.The timing of start of prone position ventilation will be determined by a team of medical personnel after determining the following: (1) the child has a stable circulation and shows no restlessness, and (2) the routine medical care has been provided.The child will be placed in the prone position with the participation of researchers, doctors, and the nursing staff. The child’s head will be tilted to one side to avoid damage to the eyes and nose due to compression; the arms will be bent upwards and placed on both sides of the head in a W-shaped configuration. The arms can also be placed in another position depending on the specific situation. Both lower limbs will be bent downwards to form an “M” shape; soft pillows will be used below both knee joints to avoid compression.Meticulous care will be exercised to ensure smooth fixation of mechanical ventilation, endotracheal tube, and various catheters.The depth of sedation will be calibrated during the entire prone position ventilation period to achieve good man-machine synchronization.Requirements during prone position ventilation: (1) adequate suction of the sputum and (2) the mechanical ventilation tube is suspended in the air, and the head is in left or right side position for 1–2 h.In a crossover design, the prone position will be maintained for 6–8 h per day until the improvement in oxygenation index (mean airway pressure × FIO_2_ × 100)/PaO_2_). Oxygenation index exceeding the baseline value or chest X-ray or CT findings suggest lung tissue recruitment. Prone position will be discontinued in case of deterioration of the condition (such as development of hemodynamic instability, pneumothorax, mediastinal emphysema, catheter loss, facial trauma, or formation of pressure ulcer).

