## Outcomes

### Outcomes (effectiveness)

Main outcome indicators: lung compliance, SPO_2_, respiratory rate, peak, positive end-expiratory pressure (PEEP); laboratory indices: oxygenation index (mean airway pressure × FIO_2_ × 100)/PaO_2_), oxygen partial pressure (PaO_2_), carbon dioxide partial pressure (PaCO_2_), pH; chest radiograph.Secondary outcome indicators: (1) duration of mechanical ventilation; (2) length of stay in cardiac intensive care unit (CICU); (3) incidence of reintubation; (4) incidence of complications: pressure skin injury, slippage of the intubation, compression, and displacement of the pipeline; (5) hemodynamic stability: heart rate (HR), invasive arterial blood pressure (ABP), central venous pressure (CVP).

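### The oxygenation index is both an entry criterion and a main outcome, but infants with mixing or right-to-left shunt circulation are neither separated nor stratified, so part of what it measures is cardiac

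*Protocol article*

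**What the plan says.** **Population.** Under Trial design the study is described as "enrolling infants with postoperative PALI after surgery for congenital heart disease". The age range is 0–12 months, and nothing limits entry to complete repair.

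**Entry.** Inclusion and exclusion criteria opens with "PALI after surgery for congenital heart disease or patients in whom chest X-ray and CT findings indicate PALI". Lung injury is then defined by three joined criteria: acute onset, bilateral infiltrates on the chest radiograph, and "2) hypoxemia, oxygenation index ≥ 4". Echocardiography appears only as one way to show haemodynamic stability, through the ejection fraction.

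**Exclusions.** The cardiac part of the table reads "Hemodynamic instability, severe hypotension, ventricular arrhythmia - Pacemaker dependent - ECMO". A later line covers delayed chest closure with wound infection. The table does not mention cyanotic, palliated, single-ventricle or residual shunt circulation.

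**Outcomes.** The abstract states: "The main outcome measures will be lung compliance and oxygenation index". The Outcomes section lists lung compliance and SpO2 among the main indicators and adds "laboratory indices: oxygenation index (mean airway pressure × FIO_2_ × 100)/PaO_2", together with PaO2 itself.

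**Treatment duration.** Under Intervention strategies, "the prone position will be maintained for 6–8 h per day until the improvement in oxygenation index". The index therefore also bears on how long prone positioning continues.

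**Randomisation and analysis.** Block randomization uses blocks of 4 (17 blocks for 68 infants) and names no stratification factor. Statistical analyses names t tests, non-parametric tests and chi-squared or Fisher tests, and no adjustment or subgroup by circulation.

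**The concern.** The hypoxaemia criterion should pick out infants whose lungs are injured and might improve with position. After surgery for congenital heart disease there is a second source of low arterial oxygen. In an infant left with intracardiac mixing or a right-to-left shunt, some venous blood reaches the arteries without passing through the lung. PaO2 is the denominator of the index, so the index is raised whatever the state of the lung.

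Two things follow. At entry, the threshold does not discriminate lung injury in these infants, and acute onset and the radiograph must do that work. At outcome, the part of the index caused by the shunt cannot be changed by recruiting lung, yet it is scored. Treatment differences in the oxygenation index, PaO2 and SpO2 are then attenuated and the spread between infants is larger. In a trial of 34 per arm, a chance difference in circulation type between arms also adds noise to these comparisons that the plan has no means of removing.

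**Working it through.** **1. Can a low PaO2 alone meet the threshold?** The formula is the protocol's: index = mean airway pressure × FiO2 × 100 / PaO2. The settings below are assumed, because the article gives none: mean airway pressure 8, FiO2 0.3.

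| PaO2 (assumed) | Index | Against the threshold of 4 |
|---|---|---|
| 90 | 8 × 0.3 × 100 / 90 = 2.7 | not met |
| 60 | 240 / 60 = 4.0 | just met |
| 40 | 240 / 40 = 6.0 | met |

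Ventilator support is identical in all three rows. A PaO2 of 40, taken here as an example of a mixing circulation, passes without any lung component.

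**2. The plan's effect size.** From Sample size/power calculation: means 276 and 228, SDs 68 and 67. Pooled SD = √((68² + 67²)/2) = 67.5, and d = (276 − 228)/67.5 = 0.71, as stated. A two-sided t test at 0.05 with d = 0.71 and 34 per arm has power 0.822. The article does not state sidedness, so two-sided is assumed.

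**3. Dilution.** Let a share f of infants show only a fraction r of the treatment effect, with the SD unchanged. The average effect size is then 0.71 × (1 − f(1 − r)). For example, f = 0.2 gives 0.71 × 0.8 = 0.568 with r = 0, and 0.71 × 0.9 = 0.639 with r = 0.5.

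| Share f (assumed) | No response (r = 0): d, power | Half response (r = 0.5): d, power |
|---|---|---|
| 0% | 0.710, 82% | 0.710, 82% |
| 10% | 0.639, 74% | 0.675, 78% |
| 20% | 0.568, 64% | 0.639, 74% |
| 30% | 0.497, 52% | 0.604, 69% |

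The column for no response is the worst case on the size of the effect. Any increase in SD from mixing two circulations is not included.

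**4. Cost of restricting the conclusion to infants without a shunt.** If 68 infants are enrolled and 10%, 20% or 30% are set aside, about 31, 27 or 24 per arm remain (30.6, 27.2 and 23.8). At d = 0.71 the power is about 79%, 73% or 67%. Compared with the worst case above this is a gain. With half response it is 79%, 73% and 67% against 78%, 74% and 69%, so there is little or nothing to gain. Restriction alone is therefore not clearly the better choice.

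**The case against.** The case on the other side is substantial, and much of it stands.

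- **The index does not admit an infant by itself.** Under the diagnostic definition, acute onset and bilateral infiltrates are also required, and a standing low PaO2 is not obviously an acute onset. A reader might infer that shunt anatomy alone brings an infant into the trial, but the definition does not support that. The protection is incomplete: the first inclusion criterion offers an imaging route joined by "or", and the criteria table words its version more loosely, around the need for pulmonary drainage.
- **A shunted infant may still respond.** A reader might infer that such infants cannot benefit measurably. An infant with both a shunt and injured lungs has a lung component that can improve. Only the shunt component is fixed, and nothing in the article shows a zero response.
- **Not every main outcome is affected.** Lung compliance does not contain PaO2. The planned paired comparison before and after prone positioning also removes much of a constant offset from anatomy, although it is not a comparison between arms.
- **The power figures rest on assumptions.** The share and the degree of response are both assumed. If the preliminary investigation behind the effect size had the same case mix, the dilution may already be in it. The means 276 and 228 also cannot be values of the index as defined, which is a separate problem, so 0.71 is used here only at face value.
- **Chance imbalance is not bias.** Randomisation balances circulation type in expectation, and the test allows for chance differences. The argument for stratifying is precision and interpretation, not validity.

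The objection that an article condenses its protocol carries little weight here, because the eligibility lists are given explicitly and the randomisation is described step by step.

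**Conclusion.** The concern holds in a limited form. Eligibility takes all surgery for congenital heart disease, and the hypoxaemia threshold and several main outcomes depend on PaO2. Neither the criteria, the randomisation nor the described analysis separates infants whose PaO2 is partly set by a shunt. In those infants the threshold does not discriminate lung injury. Their response in the oxygenation index, PaO2 and SpO2 is dampened, and they add spread.

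The size cannot be fixed from the article, because no case mix is given. For shares of 10% to 30%, power falls from 82% to between 74% and 52% with no response in these infants, and to between 78% and 69% with half response. Both ranges assume 34 per arm analysed, a two-sided t test at 0.05, an unchanged SD, and an effect size of 0.71 that does not already reflect this mix. The trial is not invalid for this reason. The weakness can be put right at low cost and should be.

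**What to change.** 1. Record circulation type at entry in two categories (mixing or right-to-left shunt, against neither), from the operation performed and the available postoperative echocardiography.
2. Stratify the existing block-of-4 envelopes by this factor.
3. Compare the oxygenation index, PaO2 and SpO2 between arms with adjustment for circulation type and for the infant's baseline value, in place of an unadjusted t test.
4. Report the stratum without mixing or shunt as a prespecified supporting analysis, not as the sole basis for the conclusion.

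This keeps all 68 infants. The cost is a second envelope series, one extra item at enrolment, and possibly one incomplete block in each stratum.

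Excluding these infants remains an option for the sponsor. It would give a cleaner oxygenation outcome at the cost of a narrower population than the trial objectives name and slower recruitment.

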**Table Taba:** 

Inclusion criteria	Exclusion criteria
**- Pediatric patients with lung injury after** surgery for **congenital heart disease or** those in whom **chest X-ray** and **CT** findings indicate the need for augmenting pulmonary drainage due to **pulmonary complications**.	-Hemodynamic instability, severe hypotension, ventricular arrhythmia - Pacemaker dependent - ECMO
**- Invasive mechanical ventilation**	-Intracranial hypertension
**-**Age range: **0–12 months**	-Active acute bleeding
**-Stable hemodynamics, more than 72 h after surgery**	-Spinal injuries and untreated unstable fractures, orthopedic surgery or recent abdominal surgery
**-Informed consent of family members**	-Facial trauma
	Severe pneumothorax
	-Patients with delayed chest closure and wound infection requiring immobilization

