### Sample size/power calculation

According to pre-experimental investigations, the average oxygenation index required by the experimental group of children is 276, with a standard deviation of 68, and the control group has an average oxygenation index of 228, with a standard deviation of 67. Comparing the two independent sample means, *α* = 0.05, *β* = 0.2, the Gpower sample calculation software showed an effect size of 0.71. The ratio of the test group and the control group is 1:1. An attrition rate of 10% has been factored in the sample size calculation. The calculated sample size is 34 patients per group and total sample size is 68 patients.

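### The eligibility text and the eligibility table define different populations: the text requires PALI with an oxygenation index of at least 4, while the table sets no oxygenation threshold

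*Protocol article*

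**What the plan says.** The protocol article states its main inclusion criterion twice.

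- **Text under Inclusion and exclusion criteria:** "PALI after surgery for congenital heart disease or patients in whom chest X-ray and CT findings indicate PALI". The next sentence defines PALI by three joint conditions: acute onset, hypoxaemia with OI of at least 4, and bilateral infiltrates on the chest radiograph.
- **Table in the same section:** the criterion opens with "Pediatric patients with lung injury after" congenital heart surgery. It then offers an alternative route for infants in whom chest X-ray and CT "findings indicate the need for augmenting pulmonary drainage due to" pulmonary complications. Neither branch mentions PALI, OI, bilateral infiltrates or acute onset.

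The other inclusion items (invasive ventilation, age 0–12 months, stable haemodynamics more than 72 h after surgery, consent) agree in substance.

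Trial design describes the study as "enrolling infants with postoperative PALI after surgery for congenital heart disease", and Trial objectives also names infants with PALI. On outcomes, the abstract states: "The main outcome measures will be lung compliance and oxygenation index". The sample size rests on OI alone.

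**The concern.** The table does not simply shorten the text. Its second route has a different object: a need for drainage instead of PALI. A ventilated, stable infant with, for example, one-sided atelectasis and OI below 4 qualifies under the table and fails the text's definition. Nothing says which statement governs.

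The conflict acts at enrolment. Under Block randomization, a researcher selects infants against the criteria and opens the envelopes. Two people working from the two statements could enrol different children.

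Two things are at stake. The first is interpretation: a trial run on the table's rule would not estimate the effect in the PALI population that the objectives name. The second is precision. On the OI formula given under Outcomes a lower value is better, so an infant who starts below 4 has little room to improve on that measure. If such infants benefit less, the between-group difference in OI shrinks. Either rule applies equally to both arms, so the disagreement does not by itself make the arms unlike each other.

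**Working it through.** **Step 1. Set the two statements side by side.**

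| Condition | Text | Table |
|---|---|---|
| Diagnosis | PALI | lung injury, or imaging-based need for drainage |
| OI of at least 4 | yes, through the PALI definition | not stated |
| Bilateral infiltrates | yes, through the PALI definition | not stated |
| Acute onset | yes, through the PALI definition | not stated |

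**Step 2. Look for an exclusion that closes the gap.** The exclusions cover haemodynamic instability, severe hypotension or ventricular arrhythmia; pacemaker dependence; ECMO; intracranial hypertension; active bleeding; spinal injury, unstable fracture, orthopaedic or recent abdominal surgery; facial trauma; severe pneumothorax; and delayed chest closure with wound infection. None concerns oxygenation or the pattern of infiltrates, so the table's route stays open.

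**Step 3. Reproduce the planning figures.** Sample size/power calculation gives 276 (SD 68) against 228 (SD 67), alpha 0.05, beta 0.2, 1:1 allocation and 34 per group.

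- Pooled SD = √((68² + 67²)/2) = 67.5.
- d = (276 − 228)/67.5 = 48/67.5 = 0.711. The stated 0.71 reproduces.
- A two-sided t test needs 33 per group for 80% power, 66 in total. With 10% attrition, 33/0.9 = 36.7, so 37 per group and 74 in total. The stated 68 fits only without the attrition allowance. That is a separate matter and is left out below by working at the stated 34 per group.

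**Step 4. Illustrate the dilution.** Let f be the share of enrolled infants with no OI benefit. The documents do not give f, so it is assumed to be 0% to 30%. The diluted effect is d × (1 − f) with the SD held at 67.5. Power comes from the noncentral t distribution with noncentrality d(1 − f)√(34/2) and 66 degrees of freedom.

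| f | Mean difference | d(1 − f) | Power at 34 per group | n per group for 80%, before attrition |
|---|---|---|---|---|
| 0% | 48.0 | 0.71 | 82% | 33 |
| 10% | 43.2 | 0.64 | 74% | 40 |
| 20% | 38.4 | 0.57 | 64% | 50 |
| 30% | 33.6 | 0.50 | 52% | 65 |

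**Step 5. Note the scale.** The planning means cannot be on the scale of the protocol's OI formula. The lower one is 228/4 = 57 times the entry threshold, and the better-performing group has the higher value. The table in step 4 therefore uses only the standardised effect and does not translate a baseline OI below 4 into planning units.

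**The case against.** The difference in wording is not in dispute. The objections concern how far it can be pushed, and most of them stand.

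- **Text's imaging branch.** A reader might infer that the words "or patients in whom chest X-ray and CT findings indicate PALI" also let infants in without OI of at least 4. The documents do not support that as the natural reading: the branch still names PALI, and the next sentence defines PALI with hypoxaemia included. The branch is ambiguous, but the conflict comes from the table.
- **Share entering by the drainage route.** Background reports pulmonary complications in 11.3% and says "the incidence of atelectasis, VAP, and lung consolidation is 8.2%, 1.4%, and 0.80 %, respectively". A reader might take 8.2/11.3 = 73% as a sign that many of the 68 would enter this way. These are department-wide incidences. They are not restricted to infants on invasive ventilation more than 72 h after surgery, and they do not say that oxygenation was normal.
- **Zero effect in those infants.** Background expects prone ventilation to help re-expand atelectatic lung and to aid sputum drainage, so some benefit in such infants is part of the rationale. Lung compliance is also a main outcome, and nothing shows that they have no room to improve on it.
- **Source of d = 0.71.** The preliminary data's eligibility rule is not given. If they were collected under the table's rule, the effect may already include the mixture.
- **Lower power figures.** At 30 per group, power is 77% undiluted and 58% or 47% at f of 20% or 30%. Those values combine dilution with loss to attrition and should not be charged to this point.

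That the article condenses a fuller protocol does not answer the point: both statements are printed, and they disagree.

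**Conclusion.** The contradiction stands. Two current statements of the main inclusion criterion define different populations, and only the text's version matches the PALI objective and design. The table permits entry without hypoxaemia to a trial sized on an oxygenation measure.

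The size of the consequence is not established. The fall in power from 82% to about 74%, 64% or 52% is an illustration. It rests on an assumed share of 10%, 20% or 30%, zero effect in that share, an undiluted d of 0.71, an unchanged SD and no attrition. It shows that the plan has little slack if dilution occurs, not that it will occur.

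A reader might also conclude that the drainage route must be deleted. The documents do not settle that. They show that the eligibility statements and the objective have to agree.

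**What to change.** 1. Reconcile the text and the table to one inclusion definition, worded identically in both places. The protocol's own three-part PALI definition is the one consistent with its stated objective. If the drainage route is intended, restate the objective and population to include it.
2. Reword the imaging branch in the text so that the three-part definition clearly applies to it.
3. Trial status says that follow-up is ongoing, and an amendment cannot change who has already entered. Keep infants already enrolled in the intention-to-treat set whichever route they came by.
4. Adjust the OI analysis for baseline OI, and pre-specify a supporting analysis in infants with baseline OI of at least 4.

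The cost is a text amendment and possibly slower recruitment if the narrower definition is kept. The stated planning effect of 0.71 does not change.
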